### Study design

This study follows is a randomized controlled trial design. Subjects (pregnant women) are the unit of randomization; they are randomly allocated to each arm of the study. Both the intervention and control group will receive usual care, but the intervention group will also receive the CDA. An independent researcher will centrally perform the randomization by using the computer program on www.randomization.com. Block randomization will be applied to ensure equal group sizes within each center. Because the study is not blinded, we use blocked randomization with randomly selected block sizes of two and four. For each center, the independent researcher will prepare opaque, sequentially numbered, and sealed coded envelopes, with a note for either the decision aid use or not. At each center, the clinic secretary will check eligibility of each pregnant woman visiting the clinic and, if eligible, will provide her with an explanation of the aims and scope of the study and will orally invite her to participate in the study. If the invitee accepts the invitation, then she will be asked to sign the informed consent form. Then the secretary writes the woman’s name and phone number on the next closed envelope. At the end of the day, all envelopes, unopened as of yet, are collected by a research assistant. At the university, this researcher assistant opens the envelopes and allocates the participants of that day to the decision aid or control group. After group allocation, the research assistant will call the participants by phone. Those in the intervention arm will be invited to a software educational session (consisting of 10 women in total) and invited to fill in the paper questionnaires. Those in the control arm will be invited to only fill in the questionnaires. All participants (in the intervention and control arms) will be invited to fill in the questionnaires again two weeks before the expected date of delivery. Blinding of researchers and women is not practical in this study, but the gynecologists are unaware of the patient allocations.

The duration of the intervention is considered from recruitment to the time of delivery. The evaluation of the intervention will be performed at 38 weeks of gestation and before delivery. We will report all cases due to premature delivery.

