### Data collection

Women are asked to complete two questionnaires: the first one upon entering the study and the second one during their 38^th^ week of gestation. Other information (related to women's health status) will be collected from pregnant women’s medical records in the hospitals and clinics.

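### The first questionnaire is completed after allocation is known, and under a different invitation in each arm, so it is not a clean pre-intervention measurement

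*Protocol article*

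**What the plan says.** All references are to the protocol article.

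Study design sets out the order of events. The clinic secretary checks eligibility, explains the study, obtains signed consent and writes the woman's name on the next sealed envelope. No questionnaire is mentioned at that visit. The sealed envelopes then leave the clinic: "At the end of the day, all envelopes, unopened as of yet, are collected by a research assistant". Only afterwards, away from the clinic, is the arm revealed, when "this researcher assistant opens the envelopes and allocates the participants of that day to the decision aid or control group". Contact with the women comes next: "After group allocation, the research assistant will call the participants by phone". Women allocated to the decision aid "will be invited to a software educational session (consisting of 10 women in total) and invited to fill in the paper questionnaires". For the others, the request is shorter: "Those in the control arm will be invited to only fill in the questionnaires". Later, everyone in both groups "will be invited to fill in the questionnaires again two weeks before the expected date of delivery". On blinding, the section says: "Blinding of researchers and women is not practical in this study, but the gynecologists are unaware of the patient allocations".

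Data collection describes the timing more briefly: "Women are asked to complete two questionnaires: the first one upon entering the study and the second one during their". That sentence goes on to name week 38 of pregnancy for the second form.

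Outcome plans to determine each woman's decision on mode of delivery before and after the intervention and to compare it with the actual delivery. Statistical analysis compares mean decisional conflict and mean knowledge scores between arms by t-test, under intention to treat, with multiple imputation for missing data. It mentions no adjustment for the first score.

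**The concern.** A first measurement serves as a reference only if the intervention, and knowledge of who will receive it, cannot have influenced it. Here it is requested by someone who knows the allocation, in a call whose content in effect tells the woman her arm. She has already heard the aims of the study, and she is either invited to a software session or not.

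Decisional conflict is self-reported, so knowing one's arm can move it. If the form is completed after the session, the knowledge score and the stated preference may also have moved. The two arms are also asked for different things, a group session plus forms against forms alone, so the proportion who complete the first form can differ.

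At stake are the before/after comparison of the delivery-mode decision, the description of how alike the arms were at the start, and any later analysis of change or with adjustment for the first score.

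**Working it through.** **Order of events.** The protocol states no figure on this point, so the check is of sequence.

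1. Consent is signed and the envelope stays sealed (Study design). No form is described.
2. The envelope is opened and the arm assigned (Study design).
3. The research assistant, who opened the envelope, phones the woman (Study design).
4. The first form is offered in that call, with the session in one arm and alone in the other (Study design).
5. The form is offered again two weeks before the due date. The word for repetition shows that the form in step 4 is the first measurement.

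No section places a form before step 2, and none says whether the form in step 4 precedes or follows the session. Data collection ties the first form to study entry, which does not say before randomisation.

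The article does not say how the initial delivery-mode decision is recorded. I assume it comes with the first questionnaire, since the only other source that Data collection names is medical records.

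**Which analyses are touched.** Let d be the true difference between arms at 38 weeks, b the difference already present in the first score because of allocation or exposure, and r the within-arm correlation of first and 38-week scores (equal to the slope if the two SDs are equal).

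- Unadjusted 38-week difference: d. It does not involve b.
- Difference in change scores: d − b.
- Baseline-adjusted difference: d − r × b.

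**Illustration.** Only the mean of 33.6 and the 15% come from the protocol (Sample size). I take d = 0.15 × 33.6 = 5.04 points. This reads the 15% as relative, although the text calls it absolute. With SD 17.6, two-sided 5% error and 80% power, the relative reading needs 192 per arm, close to the stated 200. A 15-point difference would need only 22. The share of d already present (10% to 50%) and r (0.3 to 0.7) are assumptions.

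| Share already present | b | Change score, d − b | Adjusted, r = 0.3 | Adjusted, r = 0.7 |
|---|---|---|---|---|
| 10% | 0.504 | 4.54 | 5.04 − 0.151 = 4.89 | 5.04 − 0.353 = 4.69 |
| 50% | 2.52 | 2.52 | 5.04 − 0.756 = 4.28 | 5.04 − 1.764 = 3.28 |

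The unadjusted 38-week difference stays at 5.04 in every row. The bias is towards no effect if the early shift has the same sign as the final effect. Unequal completion could act in either direction, and the documents give no basis for sizing it.

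**The case against.** The strongest reply is that the primary analysis does not use the first score. Evaluation is set at 38 weeks, the test is an unadjusted t-test, and no analysis of covariance or change score is planned. That stands. A reader might infer that the main decisional conflict and knowledge results are biased by the contaminated first form. The documents do not support this, and the losses in the table belong to analyses the article does not describe.

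A reader might also infer that the intention-to-treat comparison is broken because control women may skip the first form. That is not supported either. Nothing makes the first form a condition for remaining in the trial or the analysis, all participants are approached again near term, and missing data are to be imputed. Nor does imputing from a post-allocation score by itself bias the comparison if arm is in the imputation model, and the article does not say that the first score will be used.

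It is also fair to say that exposure before the first form is possible rather than stated, and that completion shortly after consent is loosely compatible with the entry timing in Data collection. The two sections are better described as needing one clear wording than as contradicting each other.

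What the reply does not remove is the sequence. Even if the form comes before the session, it is collected after allocation, unblinded and under different invitations.

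**Conclusion.** The point holds in limited form. As written, the measurement meant to represent women before the intervention is taken after allocation, without blinding, possibly after exposure in one arm, and with scope for unequal completion. This weakens the planned before/after comparison of the delivery-mode decision, any description of baseline balance, and any change-score or baseline-adjusted analysis that may be added. Bias in those would probably be towards no effect. Its size cannot be derived from the documents, and the range above rests wholly on assumed shifts and correlations. The unadjusted comparison of 38-week scores is not shifted. I would treat this as a cheap improvement worth making, not as a flaw that invalidates the primary analysis. Confidence is high on the order of events and low on the size of the consequences.

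**What to change.** Have every woman complete the first paper questionnaire, including her current delivery-mode decision, at the clinic straight after signing consent and before her envelope is opened. Use the phone call only to convey the allocation and, for the intervention arm, the date of the session. Reword Study design and Data collection so that both place the first questionnaire before allocation.

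Envelopes already stay sealed until the end of the day, so the randomisation procedure does not change. The cost is time at the recruitment visit: the woman has to complete the decisional conflict scale and the 15 knowledge items there, and the clinic secretary, the only person described at that visit, has to hand out and collect the forms. In busy clinics that is a real but modest burden.

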According to Orem's theory [28], decision-making constitutes a first phase of “deliberative self-care.” People who are competent at self-care and understand entirely the courses of actions are usually open to these actions and receptive to their effectiveness. Hence, improving the decision-making process by decision aids has the potential to enhance self-care. Informed decision-making can potentially reduce the over-use of expensive surgical procedures [29].

The objective of our overall project is to design, construct and evaluate a decision aid to help pregnant women choose mode of delivery. The system’s knowledge-base is obtained from the literature on cesarean delivery predictors. Our hypothesis in this study is that decision aid decreases decisional conflict and increases patient knowledge about cesarean and vaginal delivery modes. Decrease in the frequency of cesarean delivery on maternal request is a secondary expected outcome.

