### Outcome

The two primary outcomes for the study are the mean of overall decisional conflict and knowledge scores. The decisional conflict will be measured by O’Connor Decisional Conflict Scale (DCS) [25, 30]. The DCS subscales are secondary outcomes, and they will be compared between the two groups of women. The results of this study will show the specific three affected subscales in the pregnant women's decisional conflict scale. Subscale 1 addresses the uncertainty about choosing among alternatives. Subscale 2 addresses factors contributing to uncertainty, including a - feeling uninformed about the alternatives, benefits and risks; b - being unclear about personal value; c - feeling unsupported in making a choice or pressured to choose on course of action. Finally, subscale 3 addresses the perceived effectiveness of the decision [30].

The DCS scale is assessed for validity and reliability using statistical tests, including factor analysis and Cronbach alpha test. A Persian version of the scale was used in 212 pregnant women in Mashhad, Iran.

Knowledge acquisition will be evaluated by 15 true/false questions that are provided by the researchers. The actual mode of delivery, which will be measured by data obtained from hospital records after the intervention. We will determine the studied pregnant women's decision on mode of delivery before and after intervention and compare the results with the actual delivery mode. We will not evaluate cases with emergency delivery but report on them in the two groups.

The acceptability of the CDA by the enrolled pregnant women in the intervention arm will be assessed by interviewing them and analyzing open-ended comments. Our participants' experiences regarding the use of the decision aids will be reported. Also we will discuss our experience with the CDA’s implementation.

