### Statistical analysis

Differences in the primary outcomes will be analyzed using the “intention-to-treat” principle. The mean decisional conflict score and the mean knowledge score will be compared, using the t-test, to the respective means in the control group. Comparing the actual mode of delivery in the intervention and control groups will be based on hospital maternity records and differences will be tested by the Chi square test. We will calculate the Pearson correlation coefficient between the score of decisional conflict and the mode of delivery.

We will handle missing data by a multiple imputation approach. The multiple imputation procedure replaces each missing value with a set of acceptable values that represent the uncertainty about the right value to impute. These multiply imputed data sets are then analyzed by using standard procedures for complete data and then the results from these analyses are combined.

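### Ruling out blinding for all researchers leaves an undefined 'emergency' exclusion from the secondary delivery-mode comparison, and the analysis, open to knowledge of the arm

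*Protocol article*

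**What the plan says.** Study design declares: "Blinding of researchers and women is not practical in this study". The one exception it makes is for the gynecologists, who are said not to know which arm a woman is in. The same section names one person who necessarily learns the arm: "At the university, this researcher assistant opens the envelopes and allocates the participants of that day to the decision aid or control group". That research assistant then phones the women. An independent researcher generates the sequence and prepares the envelopes.

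Under Outcome, actual mode of delivery is an item "which will be measured by data obtained from hospital records after the intervention". The section adds: "We will not evaluate cases with emergency delivery but report on them in the two groups". Emergency is not defined there or elsewhere.

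Under Statistical analysis: "Comparing the actual mode of delivery in the intervention and control groups will be based on hospital maternity records". The planned test is a chi-square between the arms. Intention-to-treat is named there for the primary outcomes only.

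The delivery result is not primary. Background says: "Decrease in the frequency of cesarean delivery on maternal request is a secondary expected outcome". The two primary outcomes are the mean decisional conflict and knowledge scores, both from questionnaires the women complete.

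**The concern.** The statement on blinding treats researchers as one group. It is reasonable for those who open envelopes, phone women, run the software sessions or interview users. It is not obviously true of someone who reads a delivery record under a study number, or of an analyst.

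The distinction matters because of the emergency exclusion. Vaginal versus cesarean is an objective fact, but whether a delivery counts as an emergency decides whether a randomized woman enters the comparison at all. With no definition, no named person and a blanket statement that researchers are not blinded, the text has no barrier between knowledge of the arm and that decision. If the label were applied more readily to cesareans in the intervention arm, the apparent cesarean rate there would fall without any effect of the aid.

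Mode of delivery is also the planned between-arm comparison that does not rest on answers from unblinded women, so its protection is worth keeping.

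**Working it through.** **Step 1: who knows the arm, according to the text.**

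- Women: yes.
- Research assistant who allocates and phones: yes.
- Gynecologists: stated to be unaware.
- Person who abstracts delivery records: not named.
- Person who applies the emergency label: not named; it may be the hospital's own entry.
- Analyst: not named.

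The last three fall under the general statement on researchers unless the protocol says otherwise, and it does not.

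**Step 2: how much differential labelling would matter.** The protocol gives no figure to reproduce, so this is an illustration.

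Inputs:
- From the protocol: N = 200 per arm and a 5% type I error (Sample size). Sidedness is not stated; two-sided is taken.
- Assumed: a true cesarean rate of 50% in both arms (C = 100), 20% of control cesareans dropped as emergency, and no vaginal births dropped.

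With a fraction d of cesareans dropped, the apparent rate is r = C(1 - d) / (N - Cd).

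- Control, d = 20%: 80/180 = 44.4%.
- Intervention, d = 25%: 75/175 = 42.9%; shift -1.6 points.
- Intervention, d = 30%: 70/170 = 41.2%; shift -3.3 points.

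The standardized shift is δ = (r_I - r_C) / √[p̄(1 - p̄)(1/n_I + 1/n_C)], and the rejection rate is about Φ(-1.96 - δ) + Φ(-1.96 + δ).

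- d = 25%: p̄ = 155/355 = 0.437, SE = 0.0527, δ = -0.30; rejection 0.049 + 0.012, about 6%.
- d = 30%: p̄ = 150/350 = 0.429, SE = 0.0529, δ = -0.62; rejection 0.090 + 0.005, about 9.5%.

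A simulation with the same inputs (200,000 replicates) gave 6.0% and 9.5%. More extreme assumptions, 35% and 40% dropped, give shifts of about 5 and 7 points and rejection of about 16% and 25%.

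**Step 3: sensitivity to the cesarean rate.** Here 10 intervention-arm cesareans are dropped and none in the control arm. The first rate is the share preferring cesarean in the Mashhad questionnaire study and the second is close to the national 40.7% (both in Background). The third is assumed.

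| Rate in both arms | Intervention after dropping 10 | Shift (points) | Rejection |
|---|---|---|---|
| 26% (52/200) | 42/190 = 22.1% | -3.9 | about 15% |
| 40.5% (81/200) | 71/190 = 37.4% | -3.1 | about 10% |
| 60% (120/200) | 110/190 = 57.9% | -2.1 | about 7% |

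About ten differential exclusions out of 200 thus move the rate by 2 to 4 points. The protocol gives no basis for how many there would be.

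**Step 4: what masking would not cure.** Emergency status arises after randomization. The Discussion expects requests for cesarean to decline in women given the aid. If more of them then attempt vaginal delivery, the share who end with an emergency delivery can differ between arms for real reasons. Leaving those women out can bias the comparison even when the coder is masked.

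**The case against.** A reader might infer that unblinded researchers, perhaps those who built the aid, personally decide which deliveries are emergencies and then analyse the data. The article does not say so. It names neither coder nor analyst, and taking the mode from hospital records may simply mean copying the hospital's entry. The sentence on blinding also goes on to say that the gynecologists are unaware of allocation. If they attend the births and write the entry, the label is made without knowledge of the arm. This limits the concern but does not remove it: the article does not say that they do either, and an undefined category must still be mapped from the record.

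A reader might also infer that cesareans will be classified from records as requested or indicated, with the same exposure to bias. No such classification is planned. The stated test is actual mode, vaginal versus cesarean, and maternal request appears only as an expected outcome.

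Other points for the protocol stand. Emergency cases will be reported by group, so a gross imbalance would be visible. The tests are named in advance, which limits analytic discretion. The differential rates above are assumptions, and the mildest, 25% versus 20%, leaves the type I error near nominal. The exclusion sentence follows the one comparing women's stated decision with actual mode, so it could be meant for that comparison alone, but the text does not limit it.

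Finally, who abstracts records is a detail an article may leave to the full protocol. That would answer mere silence. Here the article makes a positive statement that researchers are not blinded, and masked abstraction or analysis described elsewhere would contradict it.

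**Conclusion.** The point holds in limited form. The statement on blinding is broader than the reason for it, and it is paired with an undefined post-randomization exclusion, so nothing in the text keeps knowledge of the arm out of the secondary delivery-mode comparison or the analysis. Bias is possible, not shown. With 200 per arm, 50% cesarean in both arms and 20% of control cesareans dropped, an intervention-arm figure of 25% or 30% shifts the rate by -1.6 or -3.3 points and raises the type I error to about 6% or 9.5%. Every input except the 200 per arm and the 5% level is assumed.

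It would be wrong to read this as a threat to the trial's main result. Decisional conflict and knowledge come from questionnaires and do not depend on how deliveries are coded.

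**What to change.** - In Study design, confine the impracticality of blinding to the women and the staff who allocate, phone, train or interview them.
- State that delivery mode and emergency status are taken from hospital records by study number, on a form without the arm, using a definition of emergency set beforehand, and locked before linkage to the allocation list.
- State that the list is held only by the independent researcher and the staff who allocate and deliver the intervention.
- Run the analysis with arms coded A/B.
- Also report the delivery-mode comparison with all randomized women, emergency deliveries included, because masking alone does not remove bias from the exclusion.

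The cost is low but not nil. Besides the change in wording, a team member not involved in allocation or training must abstract the records, and linkage to the arm waits until coding is locked. The central allocation and coded envelopes already described make this workable.

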### Sample size

We aim to detect absolute decrease of 15 % in the rate of decisional conflict between women in the intervention and control groups. A sample size of 400 pregnant women (200 per trial arm) is needed to detect this difference with a power of 80 % and 5 % risk of type I error. We used O’Connor’s Decisional Conflict Scaling method (0 to 100) to measure decisional conflict (or insecure feeling). The anticipated difference in outcome measure was based on a study assessing decisional conflict based on O’Connor's Decisional Conflict Scale of 212 Iranian pregnant women (mean 33.6; SD = 17.6) [8]. According to the O’Connor’s Scaling Method, decisional-aid tools are most effective when used for subjects with a score of 35 and above [25].

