**Methods/Design:**

The protocol concerns a randomized trial study that will be performed among Iranian women. Four hundred pregnant women will be recruited from two private and two public prenatal centers in Mashhad, Iran. They will be randomly assigned to either an intervention or a control group. The designed CDA will be provided to the intervention group, whereas the control group will only receive routine care. The CDA provides educational contents as well as some recommendations. The CDA’s knowledge base is obtained from the results of studies on predictors of cesarean delivery. The CDA’s software will be installed on women’s computers for use at home.

The two primary outcomes for the study are O’Connor’s Decisional Conflict Scale and knowledge as measured by true/false questions. Actual mode of delivery (vaginal versus cesarean) will be compared in the two groups.

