## Discussion

This study will investigate the effect of a CDA in decisional conflict of pregnant women and their knowledge acquisition pertaining to mode of delivery. This system aims to inform pregnant women and to support them in making decisions about the delivery method by addressing their concerns about the upcoming delivery. We hypothesize the CDA can decrease pregnant women’s decisional conflict and increase their knowledge about the delivery methods. We expect a 15 % effect size in the decisional conflict scale and improvement in the knowledge due to the intervention. We expect the requests for CDMR to decline due to the information and knowledge pregnant women receive through the decision aid tool provided in the study. We will investigate the difference in the DCS subscales, especially the change in the effective decision subscale, and report on that. We will also discuss the difference between the stated pregnant women's preference on mode of delivery with the actual delivery.

Some studies (McCourt [31], Mazzoni 2010 [32], and Weaver [33]) reported that only a minority of women preferred caesarean delivery, particularly in the absence of clinical indicators. We will compare our findings with these reports and discuss possible differences [31–33].

We based our work on the Ottawa Decision Support Framework (ODSF). According to ODSF, patients can be guided through multiple phases in making an informed decision regarding their social or health status. During this process, decision-support requirements are identified, designed, and evaluated. This theory suggests that women would benefit most from decision-aids that encourage a thoughtful and deliberative process. Ideally, this process should (1) increase women’s awareness of the risks and benefits of each delivery methods, (2) explain how to increase the accuracy perception of their risk, (3) assist them in evaluating the risks and benefits in the context of their personal preferences, and (4) encourage women to discuss their concerns with a health care provider [17].

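### The sample-size target (an absolute 15% fall in a rate) matches neither the primary outcome, a mean score compared by t-test, nor the 200 per arm said to be needed

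*Protocol article*

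**What the plan says.** The Sample size section of the protocol article sets the target: "We aim to detect absolute decrease of 15" per cent "in the rate of decisional conflict between women in the intervention and control groups". It continues: "A sample size of 400 pregnant women (200 per trial arm) is needed to detect this difference", with 80% power and a 5% type I error. It does not say whether the test is one-sided or two-sided. The numbers offered in support are a mean of 33.6 and an SD of 17.6 on the 0 to 100 DCS, from a survey of 212 Iranian pregnant women. The section also remarks that decision aids work best for women scoring 35 or more. It gives no baseline rate and does not define a woman as having or not having decisional conflict.

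The Outcome section states: "The two primary outcomes for the study are the mean of overall decisional conflict and knowledge scores". The Statistical analysis section compares those means by t-test. The Discussion describes the target differently again: "We expect a 15 % effect size in the decisional conflict scale". The abstract gives the number recruited: "Four hundred pregnant women will be recruited from two private and two public prenatal centers".

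**The concern.** The target is worded for a proportion, while the inputs, the outcome and the test are all for a mean. The word *absolute* adds to the difficulty: on a 0 to 100 scale, an absolute 15% reads naturally as 15 points, and for a rate it reads as 15 percentage points. If neither produces 200 per arm, the detectable effect is misstated.

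The detectable difference is the yardstick against which the result will be read. If the number was in fact chosen for about 5 points, a true benefit of 5 points would look like a failure against a stated 15, and a null result would be taken to exclude only a large effect.

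**Working it through.** **Inputs from the article.** 200 per arm, 1:1; power 80%; type I error 5%; DCS mean 33.6, SD 17.6 (all Sample size); outcome a mean, test a t-test (Outcome, Statistical analysis). **Assumed:** two-sided testing.

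**Formula for means** (normal approximation): n per arm = 2 × (1.960 + 0.842)² × SD² / δ² = 15.70 × 309.76 / δ². The t-test figures use the noncentral t distribution and come out about one woman per arm higher.

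**Formula for proportions:** n per arm = [1.960 √(2p̄(1−p̄)) + 0.842 √(p₁(1−p₁) + p₂(1−p₂))]² / 0.15², where p̄ is the average of p₁ and p₂.

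**Trying to reproduce 200 per arm.**

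| Reading of the 15% | Effect | n per arm | Power at 200 per arm |
|---|---|---|---|
| Absolute, DCS points | 15 points | 21.6 normal; 22.6 t-test, so 23 | above 99.9% |
| Absolute, percentage points, worst case | 57.5% to 42.5% | 173.2; 186.3 with continuity correction | at least 85% (no correction) |
| Absolute, taking 33.6 as a percentage | 33.6% to 18.6% | 134; 147 with continuity correction | 93% (no correction) |
| Relative to the mean | 0.15 × 33.6 = 5.04 points | 191.4 normal; 192.4 t-test, so 193 | 81.5% (t-test) |
| Relative to the score of 35 | 0.15 × 35 = 5.25 points | 177 (normal) | 84.7% (normal) |
| 0.15 of an SD | 0.15 × 17.6 = 2.64 points | 698 (normal) | 32% |

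For the fourth row: 5.04² = 25.40, and 15.70 × 309.76 / 25.40 ≈ 191.4. A one-sided test of the same 5.04 points would need 151 per arm.

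The proportion row is a ceiling. The requirement is largest when the two rates lie symmetrically about 50%, so no other baseline needs more.

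**Detectable difference at 200 per arm.** Normal approximation: 2.802 × 17.6 × √(2/200) = 2.802 × 1.76 = 4.93 points. With the t-test it is 4.94 points. Both round to 4.9.

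**Result.** Neither absolute reading gives 200. Of the readings that use only printed inputs, the 15% relative fall in the mean is the one that puts 200 per arm at about 80% power.

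**Note on loss, under the 5.04-point target only.** 193 of 200 is 96.5%, so power drops below 80% once roughly 4% of the 38-week scores are missing. At an assumed 10% loss (180 per arm) it is 77.3%.

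**The case against.** The strongest reply is that a proportion may really have been meant, and that it can be brought to 200. The Sample size section mentions a score of 35. If scores were roughly normal (an assumption), with mean 33.6 and SD 17.6, about 46.8% of women would score 35 or more. A fall to 31.8% needs 165 per arm, or 178 with continuity correction, and 178 / 0.90 is about 198 after a 10% loss allowance. Likewise 50% to 35% needs 169.3, and 169.3 / 0.85 is about 199. Both come closer to 200 than 193 does, and both keep the printed words.

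This stands to the extent that the article does not show which calculation was run. It does not rescue the wording. Each route needs a baseline rate and a loss allowance that are not printed, and each sizes the trial for a comparison of proportions, which is not the primary analysis.

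Three stronger readings are tempting but unsupported:

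- A reader might infer that the trial *was* sized for 5.04 points. That is the best-fitting reading, but 193 still has to be rounded up to 200, and neither a relative effect nor two-sidedness is printed.
- A reader might infer that the cited survey contains no basis for the 15%. The article quotes only its mean and SD, and what else it reports cannot be checked here.
- A reader might infer that the trial is underpowered because the number needed equals the number recruited. The loss rates above are assumptions, and an article commonly leaves an attrition allowance to the full protocol. The thin margin also exists only under the 5.04-point reading.

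Nor should the Discussion's "effect size in the decisional conflict scale and improvement in the knowledge due to the intervention" be taken as a standardised effect of 0.15. It looks like a loose repeat of the same 15%.

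**Conclusion.** The stated detectable effect does not agree with the stated sample size or with the primary outcome and test. Read as 15 DCS points, the plan recruits almost nine times the number required (200 against 23 per arm). Read as 15 percentage points, 200 per arm exceeds the requirement at every baseline before loss is considered. On the scale of the primary analysis, 200 evaluable women per arm give 80% power for about 4.9 points and 81.5% for 5.04 points, about a third of a literal 15-point target.

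These figures rest on the printed SD of 17.6 and an assumed two-sided 5% test. The mismatch is established; the origin of the 200 is not. The sample size itself need not change.

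**What to change.** Restate the target in the Sample size section as a difference in mean total DCS. If the sponsor confirms that this was the calculation, suitable wording is: *For a two-sided 5% t-test on mean DCS (0 to 100) with SD 17.6, 200 evaluable women per arm give 80% power to detect a difference of about 4.9 points, and 81.5% for 5.04 points (a 15% relative reduction from a mean of 33.6).* Remove *absolute* and *rate*, and state the sidedness. Bring the Discussion's 15% effect size into line.

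If a proportion was meant, give the cut-off, the baseline rate and any loss allowance, and still state the mean difference that the t-test can detect.

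The cost is a change of wording and one confirmation from the sponsor. No patients are added, and the outcome and analysis stay as they are. The stated target becomes smaller in points, which is what 200 per arm can support.
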